## Introduction

Post-stroke cognitive impairment (PSCI) is one of the vascular cognitive impairments and probably develop into dementia [1]. It was reported that 20–70% stroke survivor suffered from the cognitive impairment within 6 months after stroke attack [2, 3]. It is not only a common, important disability after stroke but also could hinder the rehabilitation of stroke-related sequelae including motor dysfunction, sensor deficits and the limited activities of daily living [4]. The pathogenesis of PSCI is multifactorial being similar with VCI. In terms of brain structure, it is generally related to focal, multifocal or diffuse cortical and/or subcortical large infarct, microinfarcts or lacunes, as which is often affected important brain areas (thalamus, frontobasal and/or limbic systems, etc.) [5]. Functionally, the PSCI is due to the disfunction of neuronal metabolism, activation and connectivity, while the exact mechanism between vascular lesion, cognition, and neuroplasticity are not completely understood [6]. Current research shows that many non-invasive neuromodulatory techniques could improve cognitive impairment via neuroplasticity [7]. As a non-invasive brain stimulation,the repetitive transcranial magnetic stimulation (rTMS) was widely used as a primary or an add-on treatment to improve cognitive function in patients with stroke [8]. Several meta-analyses confirmed its promising and positive effect on PSCI [9–11]. In these studies, mostly rTMS schemes included four primary parameters: stimulating site, frequency, intensity and pulse number, however, the rTMS intervention scheme varied substantially and the considerable heterogeneities of rTMS parameters were the great challenging in its clinical practice. Furthermore, although accumulating studies have shown that rTMS could improve the cognitive function in many neurological and psychological diseases [12, 13], the brain functional mechanism is still unclear. The present study hypothesized that rTMS could promote the cognition recovery with an optimal parameter combination and it might be objectively existed that the interaction effects between the four parameters: stimulating site, frequency, intensity and pulse number. Furthermore, we predicted that the mechanism of rTMS might be related with the neuroplasticity in three brain networks: default mode network (DMN), dorsal attention network (DAN), central executive network (CEN). Hence, the prospective, single-center, orthogonally-designed, triple-blind randomized controlled trial will be conducted and will be aimed to explore the rTMS optimum parameters regimen for PSCI based on stimulating site, frequency, intensity and pulse number and the neuroimaging mechanism in default mode network (DMN), dorsal attention network (DAN), central executive network, (CEN) following rTMS treatment in PSCI patients. All participants will be assigned averagely to one of nine paralleled active rTMS groups which are designed according to the L_9_(3^4^) orthogonal array with four different parameters: stimulating site, frequency, intensity and pulse number. This trial protocol will be written in adherence to the standard protocol items: recommendations for interventional trials (SPIRIT) 2013 guidelines [14].

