#### (4) Sample size

Because no previous orthogonally designed study provides a significant difference of MoCA or MMSE scores for rTMS treatment to PSCI, which would allow us to accurately estimate the adequate sample size for this trial, we decided to recruit 45 PSCI patients who will be randomly divided into nine groups and three subgroups based on orthogonal design (5 patients per group, 15 patients per stimulating site subgroup), in consideration of the research grant, the recruitment feasibility and the recommended sample size in neuroimaging research (medians:14.5) [17].

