#### (6) Randomization and blinding

The random numbers sequence is generated using SPSS software in computer and all eligible patients were equal assigned to one of nine active rTMS treatment group based on four rTMS parameters. The random allocation and detailed rTMS protocol are only known by the rTMS physiotherapists and blinded to physicians, patients and other researchers (such as outcome assessors, data analysts). The rTMS physiotherapists are not involved in any other study work such as patient recruitment, randomization, allocation, outcome assessment and data analysis.

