### 2. Interventions

#### (1) rTMS protocol

The rTMS treatments were delivered by a magnetic simulator (YRD CCY-I, YIRUIDE medical equipment co., LTD, Wuhan, China) with a figure-8 coil. The rTMS protocol was designed as nine combinations of four parameters at three different levels in each parameter: stimulating site (the dorsolateral prefrontal cortex, DLPFC, Brodmann areas 9 and 46; the inferior frontal gyrus, IFG, Brodmann areas 44 and 45; the temporo-parietal cortex, TPC, Brodmann areas 39 and 40), frequency (5Hz, 10Hz, 20Hz), intensity (90%, 100%, 110% of the resting motion threshold, RMT) and pulse number (1000, 1500, 2000), the detailed information are showed in Tables 1 and 2. The aforementioned rTMS parameters and different levels were predetermined based on the previous studies involving in rTMS treatment to cognition impairment duo to various neurological and psychological diseases. Once the PSCI patients were recruited, they were randomly allocated into one of nine active rTMS groups, a total of 20 sessions (four weeks, five consecutive daily sessions and two days of rest per week) active rTMS treatments with different parameters combination will be administered by two therapists with more than 5 work experience at the neuromodulating center of the rehabilitation medicine department, West China Hospital, Sichuan University. In order to improve the patient’s adherence to the intervention protocols, once every rTMS session was completed, a predesigned treatment record card should be filled and signed by the rTMS therapists and the patients or their authorized persons and ultimately returned to the study researchers.

**Table 1 pone.0271283.t001:** The orthogonal experimental factors and levels of rTMS.

Level	Experimental factor			
	A (Site)	B (Frequency, Hz)	C (Intensity, %RMT)	D (Pulse)
1	DLPFC	5	90	1000
2	IFG	10	100	1500
3	TPC	20	110	2000

Note: DLPFC: Dorsolateral prefrontal cortex; IFG: Inferior frontal gyrus; RMT: Resting motor threshold; rTMS: Repetitive transcranial magnetic stimulation; TPC: Temporoparietal cortex

**Table 2 pone.0271283.t002:** The orthogonal array L9(34).

Groups	Site (A)	Frequency (B)	Intensity (C)	Pulse (D)	rTMS protocols	Sample Size
1	TPC	5 Hz	100%RMT	1500	A_3_B_1_C_2_D_2_	5
2	IFG	20 Hz	100%RMT	1000	A_2_B_3_C_2_D_1_	5
3	IFG	10 Hz	90%RMT	1500	A_2_B_2_C_1_D_2_	5
4	TPC	10 Hz	110%RMT	1000	A_3_B_2_C_3_D_1_	5
5	DLPFC	5 Hz	90%RMT	1000	A_1_B_1_C_1_D_1_	5
6	IFG	5 Hz	110%RMT	2000	A_2_B_1_C_3_D_3_	5

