### 3. Outcomes

The primary outcomes are the Montreal Cognitive Assessment Beijing Version (MoCA-BJ) and the Trail-Making Test (TMT). The secondary outcomes are the modified Barthel index (MBI), the Lawton Instrumental Activities of Daily Living Scale (LIADL), the stroke-specific quality of life (SS-QOL), the functional magnetic resonance imaging (fMRI) scan and the adverse events. All measurements of clinical assessments were administered three times: pre-treatment (baseline), post-treatment, and at a three-month follow-up. All of the cognitive assessments were performed by a trained neuropsychologist who was blind to the treatment status of the participants throughout the study. The MRI scan were conducted at baseline and at the end of rTMS treatment.

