#### (6) ALFF and FC

The amplitude of low frequency fluctuation (ALFF) and functional connectivity (FC) will be used to explore different brain effects in the three stimulating -site subgroups.

The ALFF refers to the low frequency fluctuation of BOLD signal of the brain voxel, which will be calculated with DPARSF package after data preprocessing. The generated ALFF maps will be used for statistical analysis.

FC will be used to explore the functional connectivity changes in three brain networks (default mode network, DMN; dorsal attention network, DAN; central executive network, CEN) after treatment, which were obtained by meta-analysis (http://www.neurosynth.org/), were used as imaging indicators to analyze according to the methods described by Tomasi et al. [32]. First, Independent component analysis (ICA) will be used to extract DMN, DAN and CEN networks of the three groups, and then the brain regions with differences in the corresponding network will be found by visual observation, which will be used as regions of interest (ROI) to conduct Pearson correlation with the whole brain voxel. The FC maps obtained will be used for statistical analysis.

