### 4. Statistical analyses

The data of MoCA-BJ, TMT, MBI, LIADL and SS-QOL were shown as mean ± standard deviation (SD) and analyzed by the range analysis and one-way analysis of variance (ANOVA), which was used the SPSS 22.0 software (IBM, Armonk, NY, USA, 2020). The range analysis was used to determine the influence of each parameter at a specific level on the effect indicator and obtain the optimum combination of rTMS parameters. The one-way ANOVA was used to determine the statistical significance in nine different parameters’ combination of rTMS. P < 0.05 was considered significant.

For ALFF and FC maps, paired T-test will be used for intra-group comparison and one-way ANOVA analysis will be used for inter-group comparison in the three stimulating site subgroups. Then multiple comparison correction will be performed using Gaussian random field theory (GRF) with voxel *p* < 0.005, cluster *p* < 0.05. The Pearson correlation analyses were used to calculate the correlations between the changes in ALFF and FC with the clinical symptom scores at baseline and the end of the rTMS treatment (*p* < 0.05).

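### The between-group imaging test fits site alone, so any effect of the other three randomised parameters goes into its error term and costs precision

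*Protocol article*

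**What the plan says.** Under (1) rTMS protocol: "The rTMS protocol was designed as nine combinations of four parameters at three different levels in each parameter". Under (6) Randomization and blinding: "all eligible patients were equal assigned to one of nine active rTMS treatment group based on four rTMS parameters". The Sample size section gives the resulting numbers: "5 patients per group, 15 patients per stimulating site subgroup".

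For the clinical scales, Statistical analyses applies a range analysis to every parameter and a one-way ANOVA across the nine combinations. For the imaging maps the between-group test is narrower: "one-way ANOVA analysis will be used for inter-group comparison in the three stimulating site subgroups". The section (6) ALFF and FC takes the same grouping, saying that the two measures "will be used to explore different brain effects in the three stimulating -site subgroups". The error control is "Gaussian random field theory (GRF) with voxel *p* < 0.005, cluster *p* < 0.05". Frequency, intensity and pulse number do not appear as factors or covariates in the imaging model anywhere in the article.

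Imaging is a secondary outcome: the Outcomes section lists "the functional magnetic resonance imaging (fMRI) scan and the adverse events" among the secondary measures.

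**The concern.** A site subgroup of 15 is not one treatment. It is three arms of 5 given different frequency, intensity and pulse settings, and the trial is run because those settings are expected to matter. A one-way ANOVA on site treats the variation they cause as noise between patients. If they affect the maps, the residual is too large, the F statistic for site is too small, and real site differences are harder to detect. With only 45 patients, a number set by funding, feasibility and a typical imaging sample size rather than by a power calculation, avoidable loss of precision is worth removing.

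**Working it through.** **Inputs from the protocol.** Nine arms of 5: 9 × 5 = 45 in total and 3 × 5 = 15 per site, which reproduces the stated numbers. Voxel threshold 0.005. No imaging effect size or variance is given, so those below are assumptions, shown as a range.

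**Balance.** In Table 2 the DLPFC arms (groups 5, 7, 9), the IFG arms (2, 3, 6) and the TPC arms (1, 4, 8) each contain every frequency, every intensity and every pulse number once. All six pairs of factors show nine distinct level combinations. The same is true of the group list printed below Table 2, although its settings differ. So with equal, complete arms the site means are not shifted by main effects of the other factors.

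**Degrees of freedom.** Nine arms give 8 between-arm df: 2 for site and 6 for the other three factors. The one-way model has 45 − 3 = 42 error df, and 6 of these belong to the omitted factors. The four-factor main-effects model has 45 − 1 − 8 = 36.

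**Error inflation.** Let each omitted factor explain a share r of the variance within site. Then f² = r / (1 − 3r), and the expected one-way error mean square is multiplied by 1 + 3 × 45 × f² / 42 = 1 + 135 f² / 42. The ratio of interval widths (one-way to four-factor) is [t(42) / t(36)] × √inflation, with t(42) / t(36) = 2.018 / 2.028 = 0.995.

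- r = 0%: inflation 1; ratio 0.995.
- r = 3%: f² = 0.03 / 0.91 = 0.033; inflation 1.106; ratio 1.046.
- r = 5%: f² = 0.05 / 0.85 = 0.059; inflation 1.189; ratio 1.085.
- r = 10%: f² = 0.10 / 0.70 = 0.143; inflation 1.459; ratio 1.202.

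**Type I error.** With no site effect, the true level of the one-way test at nominal 0.05 is 0.046, 0.029 and 0.012 when each other factor has f = 0.1, 0.25 and 0.4. The test is conservative.

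**Power.** The site non-centrality is λ = 45 f_site². One-way power is the probability that [χ²(2, λ) / 2] / [χ²(42, 135 f²) / 42] exceeds the F(2, 42) critical value, found by simulation with 1,000,000 draws. Four-factor power comes from the non-central F(2, 36, λ). In each row λ is chosen to give the one-way test 60% power at 0.05 (f_site from 0.38 to 0.47), and the same λ is then used throughout the row.

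| r per omitted factor | One-way, 0.05 | Four-factor, 0.05 | One-way, 0.005 | Four-factor, 0.005 |
|---|---|---|---|---|
| 0% | 0.60 | 0.59 | 0.26 | 0.25 |
| 3% | 0.60 | 0.64 | 0.25 | 0.29 |
| 5% | 0.60 | 0.68 | 0.24 | 0.33 |
| 10% | 0.60 | 0.78 | 0.21 | 0.43 |

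The 0.005 columns are the relevant ones, because that is the plan's voxel threshold. They describe a single voxel and do not model the cluster step.

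**Aliasing.** The four main effects use all 8 between-arm df, so none are left for interactions. In both versions of the array the site contrasts have non-zero products with the two-factor interaction contrasts of the other parameters. This holds whichever of the two models is fitted.

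**The case against.** The strongest case on the other side is that this is a matter of efficiency and scope, not an error. The planned test is valid in the sense that its type I error is at or below nominal. Imaging is secondary and exploratory. Restricting it to site is a stated choice, supported in the Sample size section by comparing 15 per site with a typical imaging sample. No section promises imaging evidence on the other three parameters. The loss depends on effects the documents do not quantify: the 10% row needs the three settings together to explain 30% of variance, and if they explain nothing the larger model is marginally worse. All of this stands, and it limits the weight of the point. It does not remove it, because the precision can be recovered by a change of model at little cost.

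A reader might infer more than the documents support:

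- **That the site comparison is biased or gives too many false positives.** With complete arms the array balances the other factors over site, and the test is conservative. Dropout, which the discontinuing criteria allow for, could disturb the balance.
- **That the same scans would settle the effects of the other three parameters.** The array is saturated, and the Introduction itself expects interactions: "it might be objectively existed that the interaction effects between the four parameters". A map for frequency, intensity or pulse number can be read as a main effect only if interactions are absent. The same limit applies to site.
- **That power would rise from 60% to as much as 78%.** Those figures are at a pointwise level of 0.05. At the plan's voxel threshold neither model reaches 50% in any row of the table.

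**Conclusion.** The point holds as a loss of precision in a secondary analysis. The site-only ANOVA leaves effects of three randomised factors in the error term. Its interval is about 5% to 20% wider than necessary if each factor explains 3% to 10% of variance, and 0.5% narrower if they explain none. At the 0.005 voxel threshold the corresponding gain in power from fitting all four factors runs from about 0.04 (0.25 to 0.29) to about 0.22 (0.21 to 0.43), against a loss of about 0.01 if the factors do nothing. These figures assume 45 patients with both scans, equal effect sizes for the three omitted factors and no interactions. The direction follows from the design; the size rests on those assumptions. The change is worth making, but it will not make the imaging comparison well powered or resolve interactions.

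**What to change.** In Statistical analyses, replace the one-way ANOVA for the ALFF and FC maps with a between-group model that contains site, frequency, intensity and pulse number as main effects. Keep site as the main imaging contrast. This leaves 36 error df if all 45 patients have both scans.

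Report maps for the other three factors, if at all, as exploratory, and state that in this saturated L9 array every main effect, including site, is aliased with two-factor interactions.

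**Precondition.** Table 2 and the group list below it give different intensity and pulse settings for groups 2, 3, 4, 7, 8 and 9. They agree on site and frequency, so the planned site-only test is unaffected, but the four-factor model cannot be coded until the two are reconciled. Both versions are orthogonal, so the calculation above is the same under either.

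**Cost.** Once the settings are reconciled, a change of analysis text with no extra patients or scans. The price is 6 error df, a slight loss of power if the other factors have no effect, and more maps, with the multiplicity they bring, if the other three factors are reported.

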## Discussion

As a non-invasive brain stimulation technique, the rTMS uses high intensity magnetic field pulses to modulate neural activity and in turn modifying the brain function. Over the past few decades, rTMS is widely applied into the cognition impairment due to many neurological, psychiatrical and psychological diseases, such as stroke, Alzheimer’s disease, Parkinson’s disease, schizophrenia, obsessive compulsive disorder. Several meta-analyses and RCT have showed that the safe and beneficial value of rTMS in cognitive function rehabilitation [10, 33–35]. Given the more and more application of this method in clinical and research settings, it is crucial to understand what is the optimal parameters of rTMS for cognition impairment and how the rTMS modulates brain function via the high intensity magnetic field pulses. Fortunately, some researchers have realized these two key points. Beynel L et al. thought that the rTMS parameters include a vast composition of spatial and temporal parameters: coil geometry, stimulation target, stimulation intensity; pulse waveform, pulse train frequency, number of pulses, etc [36]. while it does not be summed precisely from the perspective of clinical application. Based on the previous literature related to multiple sessions of rTMS for cognition impairment, we hold the opinion that the most important four parameters of rTMS are stimulating site, stimulating frequency, stimulating intensity and pulse number. Orthogonal design is a powerful method for comparative effectiveness research, especially for intervention with multiple parameters, it could significantly reduce the experiment numbers and alleviate the research workloads [37]. In rehabilitation medicine, many physical modalities are delivered with a specific equipment by presetting several parameters in the meantime. It is important that these parameters should be investigated at the same time when we are going to assess the efficacy and safety of this intervention. For example, the rTMS will be delivered to a patient with cognition impairment, the stimulating site, frequency, intensity and pulses should be predetermined meanwhile. However, in the previous studies, it was common that only one parameter, such as frequency, be compared with different level, or be compared between active and sham rTMS. It is not entirely and exactly consistent with clinical practice. Hence, in order to investigate the optimum parameters of clinical value of rTMS for post-stroke cognition impairment, the present study is designed orthogonally with L_9_(3^4^) orthogonal array based four parameters with three different level in each parameter (sites: DLPFC, IFG, TPC; frequency: 5Hz, 10Hz, 20Hz; intensity: 90%RMT, 100%RMT, 110%RMT; pulse number: 1000 pulses, 1500 pulses, 2000 pulses). On the other hand, although many studies showed that the modulatory effect of rTMS on brain function, ig. enhancing the neural activity and the connectivity between different brain regions [38], is correlated to the improvement of cognition function [39], the exact neurological mechanism has not been understanded very well. Giacomo Koch et al. showed that the rTMS stimulation on precuneus enhances memory and neural activity and connectivity in default mode network [40]. Recep A Ozdemir et al. Showed that the default mode network (DMN) and the dorsal attention network brain network (DMN/DAN) specificity of rTMS activations is correlated with cognitive performance in healthy volunteers [41]. Reza Kazemi et al. showed that the bilateral rTMS stimulation on DLPFC changes resting state in CEN, DMN brain networks and cognitive function in patients with bipolar depression [42]. However, whether the brain networks related to attention and executive function (CEN, DMN, DAN) is enhanced activity and connectivity and is correlated with the cognitive improvement following the rTMS stimulation in patients with post-stroke cognition impairment are still unclear. Therefor, in the current study, the amplitude of low-frequency fluctuation (ALFF) and the functional connectivity (FC) of the resting-state fMRI signal has been adopted to reflect the regional brain network (CEN, DMN, DAN) activity and connectivity and further our understanding of the complex cognitive function recovery process underlying metaplasticity with rTMS, demonstrate how the adaptive metaplasticity can contribute to the cognition impairment, and show that whether the maladaptive metaplasticity play a role in the cognitive pathophysiology [43].

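### As written, imaging change is correlated with clinical score levels at two visits, and no correlation with change in score is planned, although the question posed is about cognitive improvement

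*Protocol article*

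**What the plan says.** Section 4 (Statistical analyses) of the protocol article plans Pearson "correlations between the changes in ALFF and FC with the clinical symptom scores at baseline and the end of the rTMS treatment", judged at p < 0.05. It does not name the clinical scores, define a change in any of them, or say whether the correlations are run in all 45 patients or within the three stimulating-site subgroups.

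The question behind this analysis is set in the Introduction and the Discussion. The Introduction predicts that "the mechanism of rTMS might be related with the neuroplasticity in three brain networks". The Discussion asks whether activity and connectivity in those networks "is enhanced activity and connectivity and is correlated with the cognitive improvement following the rTMS stimulation".

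The data for a change-with-change analysis are planned. Section 3 (Outcomes) has the clinical assessments "administered three times: pre-treatment (baseline), post-treatment, and at a three-month follow-up", and states: "The MRI scan were conducted at baseline and at the end of rTMS treatment". The participant timeline also lists a follow-up scan, but both places agree on the two visits needed here. The sample size section gives "5 patients per group, 15 patients per stimulating site subgroup".

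**The concern.** Improvement is a change, and a score at one visit is a level. A patient who rises from 10 to 18 on the MoCA and one who stays at 18 have the same end score. The baseline score measures severity at entry, and the end score carries much of that severity forward. Two errors are therefore possible if the sentence is followed as written:

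- Imaging change that depends only on how impaired the patient was at entry could correlate with both scores and be mistaken for a link with recovery.
- A real link between imaging change and improvement could be diluted in each level correlation and missed.

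This is the only planned analysis that connects the imaging results to the clinical results, so the clinical side of the mechanism aim rests on it.

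**Working it through.** The protocol gives no power, expected correlation or standard deviation for this analysis, so there is no figure to reproduce. The check has two parts: what the text says, and how level correlations relate to a change correlation.

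**Text.** In the planned sentence, the word for change attaches to ALFF and FC, and the two time points attach to the clinical scores. No other section supplies a correlation with change in MoCA-BJ, TMT or any other score. The Discussion's question concerns improvement. On the plain grammar the two do not match.

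**Algebra.** Let S0 and S1 be the baseline and end scores, dI the imaging change, and rho the correlation of S0 with S1. With equal standard deviations:

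corr(dI, S1 − S0) = [corr(dI, S1) − corr(dI, S0)] / √(2 − 2·rho)

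The planned tests examine each term of the numerator separately and do not test the difference.

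**Inputs.** From the protocol: 45 patients, 15 per site subgroup (9 × 5 = 3 × 15 = 45), alpha 0.05. Assumed: two-sided testing, a true change-with-change correlation of 0.5, rho = 0.8 (range 0.6 to 0.9). Power uses Fisher's z: Φ(atanh(r)·√(n − 3) − 1.96) plus the negligible opposite tail.

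**Severity mistaken for improvement.** Suppose dI correlates 0.5 with each score. Then (0.5 − 0.5)/√0.4 = 0, so there is no link with improvement. Each planned test would still be significant with probability 0.945 at n = 45 and 0.477 at n = 15.

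**A real link diluted.** Three sets of assumptions at rho = 0.8:

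1. Equal standard deviations, imaging change related to the scores only through score change. Here corr(S1 − S0, S1) = (1 − 0.8)/√0.4 = 0.316, so the end-score correlation is 0.5 × 0.316 = 0.16 and the baseline correlation is −0.16. Power at n = 45 is 0.18 for each.
2. Score change independent of the baseline score, with the same restriction. Here corr(S1 − S0, S1) = √(1 − 0.64) = 0.60, so the end-score correlation is 0.5 × 0.60 = 0.30 and the baseline correlation is 0. Power at n = 45 is 0.52 for the end score.
3. Equal standard deviations, imaging change unrelated to the baseline score. The end-score correlation is 0.5 × √0.4 = 0.32. Power at n = 45 is 0.56.

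Change with change at r = 0.5 has power Φ(0.549 × √42 − 1.96) = 0.945 at n = 45, but only Φ(0.549 × √12 − 1.96) = 0.48 at n = 15.

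**Sensitivity to rho**, true change-with-change correlation still 0.5:

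| rho | End-score r, case 1 | Power, n = 45 | Power, n = 15 | End-score r, case 3 | Power, n = 45 | Power, n = 15 |
|---|---|---|---|---|---|---|
| 0.6 | 0.22 | 0.31 | 0.12 | 0.45 | 0.88 | 0.39 |
| 0.7 | 0.19 | 0.25 | 0.10 | 0.39 | 0.75 | 0.29 |
| 0.8 | 0.16 | 0.18 | 0.09 | 0.32 | 0.56 | 0.21 |
| 0.9 | 0.11 | 0.11 | 0.07 | 0.22 | 0.31 | 0.12 |

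The loss runs from small (0.88 against 0.945) to nearly complete (0.11 against 0.945), depending on inputs that the protocol does not give.

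**The case against.** The strongest reply is that the sentence was meant as change in both quantities. On that reading, the word for change covers the scores as well as the imaging measures, and the two visits merely define the interval. The article's English is loose throughout, and the Discussion's wording shows that improvement was the authors' interest. This stands as a possible reading. It does not settle the matter, because no other section states it, and an analyst who ran two score-level correlations would be following the text.

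A reader might infer that the planned analysis cannot answer the question at all. The documents do not support that. Both level correlations are planned and, as the formula shows, together they carry indirect information: a baseline correlation as large as the end-score one would point to severity rather than improvement. Nor does any section say that such a result would be reported as mechanism. What remains is that neither planned test is a test of the link with improvement.

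A reader might also take the drop from 0.95 as the trial's actual loss of power. That is not supported either. Every correlation is assumed, milder assumptions give a smaller loss, and pooling to n = 45 is not stated, while the imaging comparisons are framed by site subgroup. At n = 15 the better analysis is weak as well.

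Finally, deriving a variable is often left to a fuller document. But the point here is not an omission: the article names the variables, and on their plain reading they do not match its own question. Adjustment for baseline is a preference rather than something the documents require.

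**Conclusion.** The point holds as a mismatch, or at best an ambiguity, between the planned correlation and the question it serves. Read literally, the plan correlates imaging change with score levels, and nothing in the article plans a correlation with change in score. That conclusion rests on the text alone.

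The size is illustrative. It depends on the assumed true correlation, the assumed baseline-to-end correlation, the assumptions about standard deviations and how imaging change relates to baseline, and whether patients are pooled. The gain from the correction could be large in a pooled analysis and modest within site subgroups.

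The effect is confined to the secondary imaging-mechanism aim. The primary MoCA-BJ and TMT analyses and the choice of parameter combination are untouched. It should be corrected, but it does not threaten the trial's main result.

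**What to change.** Reword the correlation sentence in section 4 to state that the change in ALFF and FC from baseline to end of treatment will be correlated with the change in MoCA-BJ and TMT over the same interval. Adjustment for the baseline score, by partial correlation or regression, is preferable. State whether the correlations are pooled or run within site subgroups. If the correlation with the baseline score is kept, label it as a separate analysis of what predicts imaging response, not as evidence of mechanism.

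The cost is one sentence and a little extra analysis. Scores and scans are already planned at both visits, so no new data are needed.
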